### Intervention

The intervention is provision of an alternative service delivery model that delivers care in a group, compared to the current standard of care provided individually (i.e., one-on-one between a provider and an ANC client). Women in the intervention arm were invited to attend five G-ANC meetings in addition to the first visit (Phase 1) and four Healthy Mother, Healthy Baby (HMHB) meetings (Phase 2) in the year following birth.

***Phase 1: G-ANC.*** At the first ANC visit (ANC1), pregnant women are assessed for GA. If eligible, women in the intervention group are offered the option of G-ANC for their subsequent ANC. Interested women are placed in a cohort of 8–15 other women of similar GA, all of whom will be 20–24 weeks pregnant at the time of a pre-scheduled cohort start date (Meeting 1). Thereafter, they attend subsequent routine visits together every month as G-ANC meetings. Five total scheduled meetings are held and recorded as ANC contacts, each lasting approximately two hours.

In each intervention facility, two ANC providers (nurses or midwives) and one CHEW were trained as G-ANC facilitators. In both countries, CHEWs are facility-based and provide some level of clinical care. Two facilitators were assigned to each cohort and were advised to co-facilitate meetings for that group throughout the intervention.

Prior to initiating the study, inputs were made to all facilities, in both arms, in the same quantities, to ensure comparable capacity for service delivery (
Table 3). The inputs included a select set of ANC commodities that would ordinarily be provided through the public sector health system. In addition, a one- to two-day refresher training on ANC and PPFP counseling was provided for all ANC providers at control sites and for G-ANC facilitators at intervention sites. Intervention facilities received additional G-ANC specific inputs as outlined in
Table 3.

**Table 3. T3:** Inputs provided to control and intervention clusters. Description of the elements of support provided to the two study arms in accordance to the group assignment.

Input	Intervention Clusters (Group Care)	Control Clusters (Current Standard Individual Care)
**Provision of key ANC commodities:** LLIN; intermittent preventive treatment in pregnancy for malaria using sulfadoxine-pyrimethamine (IPTp-SP); iron and low dose folic acid (IFA) tablets; HIV test kits; syphilis test kits; urine dipsticks; three CRADLE Vital Sign Alert automatic blood pressure devices per facility	X	X
**One- to two-day ANC and PPFP counseling update for ANC service providers**	X	X
**Five-day PPFP clinical training (inclusive of postpartum intrauterine device [IUD] and implant** **insertion and removal) followed by clinical practice**	X	X
**Five-day G-ANC training for facilitators** in logistical planning and facilitation of G-ANC for two ANC providers and one CHEW per facility	X	
**Four-day HMHB training for facilitators**	X	
**G-ANC and HMHB specific materials:** facilitator’s guide, large illustration cards, self-assessment cards and markers, women’s take-home booklets, longitudinal group cohort registers, privacy screens, chairs	X	
**Tea/snacks during group meetings**	X	
**Ongoing mentoring** specific to group care by study staff (i.e., goal of attending 80% of meetings of first two cohorts)	X	
**Debriefing tools,** including fidelity and facilitation skills checklists to be used by mentors and as self-evaluation by G-ANC facilitators	X	
**Mobile phone credit (air time) for reminder calls to women prior to group meetings**	X	

* Where inputs identical, they were provided during similar time periods and in equal quantities

Clinical care in both study arms was provided according to national clinical standards and guidelines
^47–
50^. No changes were made to clinical care protocols or content in any health facility. No additional activities were undertaken in either arm to improve the quality of clinical care (e.g., support for management of complications; integration of PPFP in postnatal wards). The curriculum content was divided into five sessions during antenatal care visits and four sessions for antenatal visits in the intervention arm (
Table 4).

**Table 4. T4:** G-ANC and HMHB meeting content. Summary of activities and content covered during each group meeting before and after delivery.

Meeting	Timing and Content	
**G-ANC**		
**Meeting 1**	**20–24 weeks GA** • Introduction to group care • Preventing problems in pregnancy	
**Meeting 2**	**24–28 weeks GA** • Recognizing problems in pregnancy • Partner negotiation and communication (e.g., sexually transmitted infection prevention)	
**Meeting 3**	**28–32 weeks GA: Partners encouraged to attend** (if group agrees) • Birth planning • Healthy timing and spacing of pregnancy and PPFP method options	
**Meeting 4**	**32–36 weeks GA** • Review individual birth plans and PPFP intent • Preventing problems after birth (maternal and newborn) • Labor signs	
**Meeting 5**	**36–40 weeks GA** • What to expect in labor and birth • Recognizing postpartum problems (maternal and newborn)	
HMHB		
**Meeting 1**	**3 months after** **delivery**	Clinical care is offered to babies and mothers at every meeting. Each meeting covers similar topics with content specific to the age of the baby: **Raising Baby** • Understand your baby: Developmental milestones; responsive and positive parenting • Maximize love and learning: Four age-appropriate activities for early childhood development are demonstrated and practiced, including one picture-based, early literacy activity, in each session • Feed and protect: Three to four specific topics covering: nutrition; water, sanitation, and hygiene practices; accident prevention; and well-baby care (e.g., immunizations, vitamin A, use of oral rehydration salts) **Taking Care of Yourself** • Self-care activities: Recognizing postpartum depression; postpartum exercise/pelvic floor rehabilitation; getting rest; asking for help • PPFP: Sharing experiences and knowledge; partner challenges; management of side effects
**Meeting 2**	**6 months after** **delivery**	
**Meeting 3**	**9 months after** **delivery**	
**Meeting 4**	**12 months after** **delivery**	

At the first meeting, women agreed on what day and time they would like subsequent meetings to be and whether husbands should be invited to Meeting 3 (
Table 4). Women who have or develop complications requiring additional individual care are encouraged to continue attending group meetings.

Longitudinal group care registers were introduced in the intervention facilities and used for each cohort. They serve a dual purpose of data collection and reinforcement of key actions by providers and women, such as taking IFA supplements, sleeping under a LLIN, birth planning, and making plans regarding healthy timing and spacing of pregnancy.

***Phase 2: HMHB.*** Healthy Mother, Healthy Baby meetings extend group care into the first year after birth (
Table 4). The same cohorts continue to meet, with their babies. Meetings are scheduled every three months (total of four HMHB meetings). Because of the staggered timing of births for women in a cohort, HMHB meetings are not designed to replace standard PNC visits (i.e., four visits in the first six weeks) as recommended by WHO and included in national guidelines of both countries
^51^. Women in both arms are encouraged to follow country guidelines regarding immediate PNC, as well as national immunization schedules (when they do not correspond to scheduled group meetings).

In 2017, the G-ANC facilitators were trained to facilitate HMHB meetings and remained attached to the same cohorts in the intervention arm. Prior to the first cohort delivering, two to three providers from each facility in both arms will receive clinical training in PPFP methods.

***Meeting frameworks and key content.*** The meeting frameworks for G-ANC and HMHB were designed to incorporate three key components of group care: 1) individual clinical assessment; 2) participatory, facilitated learning, and; 3) peer support. The frameworks were informed by evidence-based learning principles, social behavior change and communication principles, and social support theories. They were designed to include highly facilitative, nonhierarchical, patient-centered participatory approaches with attention to education and literacy levels and community cultural norms.

Clinical assessments include self-assessments (e.g., blood pressure, weight, and danger signs), and brief, individual, private assessments with the provider, behind screens within the group meeting space. To address the main topic of each meeting, large illustrations cards are used to facilitate discussion around key actions or danger signs. Questions are posed to the group while viewing each illustration to: promote sharing of knowledge, examine cause and effect, agree on actions to take, discuss barriers and solutions, and agree to share information with others. The women receive take-home booklets with small versions of the same illustrations to use as memory aids and resource guides for sharing information with family and friends. Other meeting components are designed to specifically support group identity and cohesion; promote empowerment, self-efficacy, and agency; and promote self-reflection and planned action.

### Training and mentoring

Prior to introducing G-ANC in the intervention sites, 30 facilitators in each country were trained together by study staff in a five-day workshop offsite using the G-ANC framework and materials developed for this study. They were also trained to use self-reflective quality assurance and improvement tools, which included a scorecard for facilitation skills, a fidelity checklist, and prompts for identifying strengths and weaknesses and things to change or try at the next meeting.

Program officers (POs) were employed by the study to mentor facilitators, oversee research assistants, and support daily implementation of the study at all study facilities in their defined geographic area. POs are nurse-midwives who speak the local languages. POs aimed to attend 80% of the first three cohorts at each facility to provide mentoring on the G-ANC model and feedback on facilitation skills. Debriefs immediately after group meetings followed a structured coaching outline, incorporating reflections from the G-ANC facilitators.

### Outcomes

Different outcomes are targeted for the different phases of the trial. The primary outcome for Phase 1 is the proportion of facility-based delivery among women enrolled in intervention (G-ANC) arm versus control (standard individual care) arm. For Phase 2, the main outcome is the proportion of women using a modern FP method (defined for study purposes as condoms, oral contraceptives, injectables, implants, IUDs, and sterilization) at 12 months postpartum, comparing the two study arms.

Secondary outcomes include additional measures of: service utilization; provision of quality ANC; experience of care by women and providers (measures of satisfaction and positive experience); MNCH/FP-related health literacy and uptake of healthy behaviors (e.g., sleeping under a LLINs, taking IFA supplements, early initiation of breastfeeding, knowledge of danger signs, knowledge of lactational amenorrhea method criteria); and improvement in agency, self-efficacy, and empowerment, specifically related to birth planning and PPFP (
Table 5).

**Table 5. T5:** Research questions and outcomes by study phase. Study research questions, outcomes and data collection tools stratified by study phase (1&2).

Research Questions	Secondary Research Questions
**Outcomes are cross-referenced with the data collection tools used to answer the question (in parentheses)**	
**PHASE 1: G-ANC**	
1. Are women in G-ANC arm more likely to deliver in a health facility, compared to women who are allocated to standard individual ANC? ( 4, 5) **Phase 1 primary outcome:** Health facility delivery	Are women allocated to G-ANC more likely than those allocated to standard individual care to: 1. Attend 4 or more ANC visits ( 4, 5) 2. Receive better quality provision of care as measured by: a. Total average doses of IPTp ( 5) b. Frequency of danger sign assessment at every visit ( 4) c. Total percentage of ANC visits with blood pressure recorded ( 5) d. Frequency of patients who received counseling on 12 key topics ( 4) 3. Report greater satisfaction and improved experience of care ( 4, 7) 4. Increase health literacy and practice of healthy behaviors ( 4, 7) 5. Report greater agency, self-efficacy, and empowerment, as measured by: a. Completion of birth plans ( 4, 5)) b. Choice of PPFP method prior to delivery ( 4, 5) Do providers report improved satisfaction and enjoyment and prefer providing G-ANC to standard individual care? ( 1, 3, 6)
**PHASE 2: HMHB**	
2. Are women in G-ANC more likely to be using a modern FP method at one year postpartum, compared to women allocated to standard individual care? ( 9) **Phase 2 primary outcome:** Use of a modern FP method at 12 months postpartum	At one year postpartum, are women allocated to G-ANC more likely than those allocated to standard individual care to: 1. Have attended more clinic visits, resulting in a. Higher average number of growth monitoring measurements ( 9, 10) b. Fully vaccinated infants ( 10) 2. Exhibit increased health literacy and practice of healthy behaviors, including: ( 9) a. Creation and use of hand washing station b. Exclusive breastfeeding until 6 months c. Earlier introduction of animal-based proteins d. Practice of select early childhood development activities by multiple members of household 3. Report increased couple communication and agreement in relation to healthy timing and spacing of pregnancy ( 9, 11, 12) 4. Report greater satisfaction and improved experience of care ( 9, 11, 12) 5. Report greater agency, self-efficacy, and empowerment in part measured by: a. PPFP self-efficacy scale ( 9) Do health care providers report improved satisfaction and enjoyment and prefer providing HMHB meetings to standard individual care in the first year postpartum? ( 11)

**Numbered data collection tools:** 1: ANC baseline survey; 2: survey of recently delivered women; 3: data extraction tool (from G-ANC registers and health facility records); 4: focus group discussion (FGD) guide for pregnant women in the intervention group at completion of G-ANC meetings; 5: in-depth interview (IDI) guide for pregnant women, at completion of group care before delivery; 6: IDI guide for health care providers (after completion of group care before delivery); 7: IDI guide for sub-national health managers (after completion of group care before delivery); 8: women's survey at one year after birth; 9: data extraction tool (from HMHB registers and health facility records); 10: IDI guide for women, at completion of group care, approximately 12 months after delivery; 11: IDI guide for health care providers (after completion of group care, approximately 12 months after delivery); 12: IDI guide for sub-national health managers (after completion of group care)

### Recruitment and consent

All ANC service providers at all study sites were oriented to the study prior to initiation of enrollment. Enrollment ended January 2017 in Nigeria and June 2017 in Kenya. One research assistant (RA) was hired and assigned to each health facility in both study arms. Standardization of study procedures was facilitated by a study manual (
Supplementary File 1), which was provided to all study staff.

***Health care providers.*** Study staff approached eligible ANC and PNC health care providers in participating health facilities, explained the purpose of the study, and obtained written consent prior to starting study enrollment. Health care providers were not blinded to group assignment. In intervention sites, two health care providers and one CHEW were recruited. In control sites, all health care providers who provide ANC services were included.

***Pregnant women.*** Research assistants were stationed at their assigned site during ANC service provision. ANC providers documented GA, methods used to calculate GA, and estimated date of delivery for every new ANC client. Those < 24 weeks GA were referred by the ANC provider to speak to the RA for further eligibility screening. No personal identifiers were retained for clients > 24 weeks GA, or those who did not ultimately consent.

Each RA conducted screening and consent in a location in the facility that allowed for audio and visual privacy. Women were accorded an opportunity to hear more about the study through use of a client study information sheet and screening was done in the most appropriate of five languages (English; Kiswahili, Kamba, and Luo in Kenya; English and Hausa in Nigeria). After confirming eligibility, the RA then collected basic demographic data. No personal identifier information was collected prior to the consent process.

In the intervention arm, assignment to a cohort was done based on GA at the time of the pre-determined cohort start date (i.e., Meeting 1). Eligible women unable to attend the first meeting were not consented or assigned to a group; they were advised to continue with standard individual ANC. If a woman was eligible for the study, but there were no open cohorts (e.g., the appropriate cohort was full), she was advised to continue with standard individual ANC. In the control arm, all eligible women who were willing to participate were consented. Written consents were obtained for all study participants in their language of choice (from the five options). A baseline survey was administered immediately after the consent process.

If it was not possible to recruit a minimum of eight women at least three days before the scheduled cohort start date, the cohort was cancelled, and the assigned women re-evaluated for eligibility into another cohort. Women who become ineligible to participate due to cohort cancellation were advised to continue with standard individual ANC. Their data were then coded to reflect cohort cancellation and retained for reporting purposes. However, they were removed from the study sample, and no additional follow-up was done for these women.

***Sub-national health managers and health facility in-charge.*** Sub-national health managers (i.e., county-level in Kenya; state-level in Nigeria) responsible for overseeing reproductive health programs were recruited by study staff via phone at the end of Phase 1 to participate in the in-depth interviews (IDIs). Priority was given to managers known to have had exposure to G-ANC at the end of Phase 1. An appointment for a face-to-face interview was scheduled with each respondent.

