Group ANC (G-ANC) is an alternative ANC service delivery model. Where implemented, G-ANC is described and offered as an alternative to individual care when women come to their first ANC visit. Women who choose G-ANC are placed in groups, or cohorts, with other women of similar gestational age (GA) and receive subsequent ANC together during scheduled meetings facilitated by a health care provider at the health facility. Implementation and research on G-ANC to date has primarily been in high-income countries
^22,
23^. These studies found that, when compared to individual ANC, G-ANC resulted in increases in several outcomes: uptake of family planning at 6, 9, and 12 months postpartum; length of gestation; birth weight; breastfeeding initiation and duration; attendance at ANC; health literacy; and patient satisfaction; as well as decreased transmission of sexually transmitted infections during pregnancy
^24–
26^. A Cochrane review in 2015 was not conclusive on the health outcomes of the intervention, however, it found participants viewed G-ANC positively, and no negative outcomes for mothers or their babies were identified
^27^.

This evidence was considered by the World Health Organization (WHO) in the development of new ANC recommendations in 2016. Those recommendations state that G-ANC may be offered as an alternative to individual ANC in the context of rigorous research
^2^. To date, there have been a limited number of studies on the effect of G-ANC in LMICs, primarily from single site studies in Malawi, Tanzania, Nigeria, and Ghana
^28–
34^. Available results indicate acceptability and feasibility, but the single site nature of these studies limits generalizability.

We therefore designed a cluster randomized controlled trial (cRCT) to test the feasibility, acceptability, and effectiveness of G-ANC in multiple facility contexts, including a mix of urban, peri-urban, and rural sites, in two African countries. The cRCT design enables implementation in sites with lower ANC census numbers than would be necessary for an individually randomized study (i.e., twice the census would be needed to form cohorts while individually randomizing). In addition, the cluster design decreases the risk of contamination between study arms.

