**Pregnant women**	• Minimum age of 15 years at the time of enrollment * • Appropriate GA as best estimated by provider using combination of last menstrual period, pelvic exam, fundal height, quickening, ultrasound, and/or timing of fetal heart tones dependent on availability o Control sites: < 24 weeks GA o Intervention sites: Between 20–24 weeks GA at the time of first group meeting; and reply “yes” or “unsure” when asked if can return for first cohort meeting • Willing and able to provide a phone number through which she can be reached • Detailed locator information for follow-up (all who provide cell phone number AND also for those without cellphone but traceable). • Planning to stay in area for the next year, and not planning to be away from home (near this facility) for more than four weeks in a row at any time during pregnancy or more than three months in a row in the year after the baby is born • Willing to participate and consent to follow-up for up to 12 months post-delivery
**Health care** **providers**	• Working in a participating/selected health facility and providing ANC or PNC services • Willing to participate in the study
**Sub-national health** **managers**	• Working in the study state or county as a government official managing health activities and/or service delivery • Willing to participate in the study

*Note, In Kenya, pregnant women under the age of 18 are considered mature minors and are able to give consent for themselves, if they can demonstrate evidence of clear understanding of the requirements for the research they are consenting to participate in Kenya
^45^. In Nigeria, persons aged 13 and above can consent for themselves (i.e., without parental consent) to participate in non-therapeutic research
^46^.

***Eligibility for participants.*** Study participants include pregnant women, health care providers, and sub-national health managers. The inclusion criteria are detailed in
Table 2. There were no additional exclusion criteria.

**Pregnant women**: Pregnant women 15 years and older attending ANC1 in any of the study health facilities. Additional criteria on GA and availability were applied depending on the study arm.

**Health care providers:** Providers working in the participating health facilities primarily providing ANC and PNC services.

**Sub-national health managers:** Included either government officials who work in sub-national level health management positions or health facility in-charge in study settings.

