## Discussion

The authors are not aware of any previous cRCTs on G-ANC or postpartum facility-based group care in Africa. The study will contribute to the body of evidence that will inform decision makers locally and globally on whether G-ANC is a feasible service delivery model that is more acceptable and effective than individual ANC. It will similarly inform stakeholders if continuing those cohorts is feasible and of sufficient value to implement. The findings of this study are expected to inform decision-making at different levels on whether to adopt the model as matter of policy, and how group care can be integrated into routine service delivery.

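### Women's satisfaction is measured only after intervention sites have filtered on interest in group care and ability to attend, so it cannot support a more-acceptable conclusion for antenatal clients in general

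*Protocol article*

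**What the plan says.** The Background and study rationale section gives the purpose of the trial as "to test the feasibility, acceptability, and effectiveness of G-ANC in multiple facility contexts". The Discussion says the evidence will inform decision makers "whether G-ANC is a feasible service delivery model that is more acceptable and effective than individual ANC", and the section on dissemination repeats this. Neither place limits the statement to women who chose a group.

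Entry to the intervention arm is described in three places:

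- **Intervention, Phase 1:** "women in the intervention group are offered the option of G-ANC for their subsequent ANC", and then "Interested women are placed in a cohort of 8–15 other women of similar GA".
- **Table 2, intervention sites only:** a woman must "reply “yes” or “unsure” when asked if can return for first cohort meeting".
- **Recruitment and consent:** "Eligible women unable to attend the first meeting were not consented or assigned to a group". Women for whom no suitable cohort is open are sent back to individual care. Women who lose eligibility because a cohort is cancelled leave the sample and are not followed.

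Control facilities consent all eligible women who are willing to take part.

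In Table 5, the measures among women that bear on acceptability are satisfaction and experience of care, in both phases. Table 6 shows the women's surveys in both arms, and the women's focus groups and in-depth interviews in intervention facilities only. Table 5 also asks about providers' satisfaction and preference, and health managers are interviewed.

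**The concern.** A woman who hears about group care at her first visit and does not want it, or cannot come at the set time, has given direct evidence on whether the model is acceptable or feasible for her. Under the entry rules she is gone before anything about acceptability is measured. What remains is satisfaction given acceptance, which could be high whether few or many eligible women turned the offer down.

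The filter also works in one arm only and after the facility's allocation is known, so the satisfaction comparison is between differently selected women. A policy maker reading that group care proved more acceptable would naturally apply this to women attending antenatal care, and the planned measures among women do not reach that population. This is separate from balance between the arms on facility delivery or family planning: it concerns whether a stated aim is answered.

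**Working it through.** The plan gives no figure on this point, so the check is mainly a comparison of sections.

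**Step 1. Population of the intended conclusion.** The Background and the Discussion state a comparison of two service models, without restriction to women who opted in.

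**Step 2. Who is enrolled.**

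| Filter | Intervention | Control |
|---|---|---|
| Willing to take part in the study | Yes | Yes |
| Interested in group care | Yes | None |
| Answers that she can return, or is unsure | Yes | None |
| Not unable to attend Meeting 1 | Yes | None |
| A suitable cohort is open | Yes | None |
| Cohort not cancelled, or woman can be moved to another | Yes | None |

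The first three intervention-only filters depend on the woman's attitude or circumstances. The last two depend on logistics and bear on feasibility.

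**Step 3. Where acceptability among women is measured.** Satisfaction and experience are surveyed after enrolment. The interviewees closest to a dissenting view are women who joined but came to only one or two meetings; they had still accepted the offer. Recruitment and consent says no identifiers were kept for women who did not consent, so women who declined cannot be traced now.

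**Step 4. Whether any outcome counts the offer itself.** Table 5 lists none. Analysis by randomized arm does not help, because women who declined never enter the data. Adjusting for baseline characteristics cannot replace an unrecorded refusal.

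**Step 5. Form of the bias in the satisfaction comparison.** Let s be the share of otherwise eligible women who would pass the intervention-only filters. Let a be the satisfaction proportion in those who would pass and b in those who would not, and let g = a − b. Suppose group care changes nothing.

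- Intervention arm observed: a
- Control arm observed: s·a + (1 − s)·b
- Difference: a − s·a − (1 − s)·b = (1 − s)·g

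Neither s nor g is in the documents. With assumed values of g from 10 to 30 percentage points:

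- s = 0.9: 0.1 × 10 to 0.1 × 30 = 1 to 3 points
- s = 0.7: 0.3 × 10 to 0.3 × 30 = 3 to 9 points
- s = 0.5: 0.5 × 10 to 0.5 × 30 = 5 to 15 points

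These values show only how the bias depends on take-up. They do not estimate it for this trial, and a negative g would reverse its sign.

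**The case against.** **Group care is an opt-in model.** The Background describes it as an alternative for women who choose it, so experience among choosers is a legitimate question. This stands, and it is why the satisfaction results keep their value. It does not stretch to an unrestricted claim of greater acceptability.

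**The article does not define acceptability, and the enrolment flowcharts may already count women who declined.** Figures 2 and 3 are not shown, so this may be so. Even then, Table 5 does not name those counts as an outcome. Their existence would make the remedy easier.

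**Several stronger readings are tempting but not supported:**

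- *A reader might infer that the trial can say nothing about acceptability.* It can describe joiners' experience, it plans interviews with low attenders, and provider and manager views do not pass through the filter on women.
- *A reader might infer that only women certain to come were admitted.* Those who were unsure were eligible.
- *A reader might see a defect in holding women's focus groups and interviews in the intervention arm only.* Control women have no experience of group care, and the between-arm comparison uses the survey given in both arms.
- *A reader might multiply an assumed satisfaction rate by an assumed take-up rate and call the product true acceptability.* Neither input is documented, and the product would count a clash with the meeting date as rejection of the model.
- *A reader might expect take-up to prove group care more acceptable.* It is observed in one arm, with no control counterpart, so it cannot.

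**Reasons for non-enrolment may not have been recorded.** The article does not say that they were. Basic demographic data were collected only once eligibility was confirmed, so a woman who answered no about returning may have left little trace. This limits the detail of the remedy, not the need for it.

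**Conclusion.** The concern holds within limits. Intervention sites enrol women who have shown interest in group care and are not unable to attend Meeting 1, while control sites apply no matching filter. The planned measures among women therefore describe experience among those willing and able to join. They cannot support a conclusion that group care is more acceptable than individual care for antenatal clients in general, and the between-arm satisfaction difference may be biased by the one-arm selection.

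No numerical size can be given from the documents, because neither the take-up share nor the satisfaction of women who did not join is available. The conclusion rests only on the stated entry rules and the outcomes listed in Table 5.

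**What to change.** Enrolment is complete, so the change is to analysis and reporting.

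1. Add an acceptability and feasibility outcome beside satisfaction: take-up of group care and attendance at Meeting 1, among otherwise eligible women at intervention facilities. Use the enrolment-cascade counts.
2. Show separately the women who declined, could not attend, found no open cohort, or had their cohort cancelled. Cancellations were coded and kept for reporting. Where the records do not separate the other reasons, or mix refusal of group care with refusal of research, report a combined category and say so.
3. State that the satisfaction and experience results apply to women willing and able to join a group, and that the difference between arms may be biased by selection in one arm.
4. Do not conclude that group care is more acceptable than individual care for all antenatal clients.

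The cost is a table from whatever screening counts exist and narrower wording, with no new data collection. The downside is a less favourable and more limited acceptability statement.
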